#### Bimanual Occupational Therapy

The bimanual occupational therapy (BOT) was underpinned by components of motor learning [102] and cognitive-based motor intervention [103,104]. This eclectic approach to treatment is commonly adopted by occupational therapists in the training of upper limb motor skills in children with cerebral palsy [30]. Details of the components adopted from motor skill acquisition, motor learning and motor control theory, the Assisting Hand Assessment hierarchy and cognitive based approaches are described below.

##### Motor skill acquisition, motor learning and motor control theory

Practical application of a *motor learning *framework requires implementation of a motor-teaching model whereby the therapist acts as a teacher and the child, a learner. Factors required to facilitate a child's learning of motor skills include: giving attention to the context; motivation and prior knowledge; instructions; modelling; taxonomy and sequencing of tasks; anticipation skills; mental and physical practice; repetition; facilitation-guidance; and feedback [102]. Similar core components have been outlined for improving motor skills in children using a *motor skills acquisition *frame of reference [27]. These frameworks [27,102], along with more recent advances in the knowledge of motor planning difficulties experienced by children with cerebral palsy [30,105], formed the core components of the BOT provided in this RCT. Examples of the practical implementation of these principles included:

• Initial and ongoing task analysis to identify if the child's performance was limited by execution of movement or motor planning difficulties (i.e. sequencing of movements) [30,105,106]. Motor planning impairment was observed by presenting a child with a novel task without prior modelling or task demonstration. It is evident when you know the child has the underlying physical capacity to complete the task but they simply cannot organise or plan the sequence of actions or required movements of the hands to successfully perform the task.

• Repetitive whole-task practice of challenging, motivating and purposeful bimanual activities (i.e. toys and games), carefully selected to facilitate learning and development of goal-based skills and independence with task completion [101].

• Use of modelling, physical assistance, verbal cues or environmental adaptation to enable the child to understand the critical features of the task and the environment.

• Facilitation of the child's learning and understanding of the role of their assisting hand (i.e. hemiplegic hand) using active problem solving.

• Grading of physical and/or verbal assistance provided to complete tasks.

• Provision of feedback focusing on the outcome, task and environment rather than specific movement performance.

• Provision of opportunities for the child to repetitively practice tasks in a range of contexts and environments.

##### Understanding and grading task difficulty in bimanual intervention

The Assisting Hand Assessment (AHA), designed specifically for children with unilateral impairment, was developed using a Rasch measurement model. This model allowed identification and ordering of the AHA test items on a scale from easiest to hardest. For example, simply approaching an item using the affected hand (easier item) to using in-hand manipulation skills to move objects in the affected hand (more difficult item). Based on the Rasch model, easier items are more likely to be easier to perform for all children than more difficult items. More able children are also more likely to perform better on more difficult items than less able children. The unique construct allows children's bimanual upper limb ability levels to be placed along a continuum of low ability to high ability. This knowledge can be used to design intervention and guide graded task performance [107]. For example, attempting to improve the bimanual performance of a child with low ability to place objects directly onto a table (most difficult item) using the assisting hand is inappropriate. Treatment for this child should focus on the development and consolidation of easier items such as holding objects or stabilising by grip. Conversely, continually focussing on easier items for a child with high abilities will not serve to improve their abilities on more difficult items. In this RCT, although specific details of the AHA scores remained unknown to the treating therapist, knowledge of the AHA hierarchy served as an important guide for selecting specific activities during the implementation of BOT. Treatment was tailored to the individual child based on their typical performance in the initial treatment sessions (see Figure 3).

**Figure 3 F3:**
[figure not shown]
**Using the Assisting Hand Assessment hierarchy to grade treatment**. DH = Dominant Hand; AH = Assisting Hand

##### Cognitive approach

Children with hemiplegic cerebral palsy have varied abilities to perform bimanual activities. Often children have the underlying motor abilities (i.e. adequate range of movement, ability to grasp, hold and release) to execute the required movements for task performance, however they are unable to independently identify the specific role for each hand, appropriately position the hands and object or sequence the movements or direction of force required to complete the task. These motor planning difficulties may be just as limiting for the performance of activities of daily living as is movement execution in children with cerebral palsy [105].

Cognitive-based approaches [103,104] have evolved and been adapted for use in approaches such as Cognitive Orientation to daily Occupational Performance (CO-OP). Developed in the 1990's for the treatment of motor disorders in children with DCD [88,108], CO-OP is a task oriented problem-solving approach that utilises cognitive skills to improve occupational performance [109]. The child is guided to develop his/her own strategies based on problems encountered during a task. In this RCT, the bimanual approach to training was grounded in cognitive-based intervention theory. Much of the treatment targeted the motor planning abilities of children with both low and high bimanual abilities. Children engaged in a self-instructional training program that was carefully facilitated by the treating therapist [110]. In the context of this RCT, the treating therapist reinforced to children that the difficulties they often experienced with task performance was because they were not taking advantage of certain strategies or tricks that they could learn [110]. Novel activities were chosen which the child could only solve by carefully looking and listening, and for which a plan or strategy was required before any movement or action took place (e.g. pushing plastic links together). Attempts were made to encourage the child to plan ahead and reduce impulsive tendencies to quickly grab the object using their dominant hand before they thought about the role of affected hand in the task. Before handing the toy to the child, the therapist demonstrated exactly what was involved to complete the task. The therapist modelled the required movements and emphasised important sequences and strategies whilst verbalising these aloud using simple, key words. Deliberately, the therapist occasionally performed components of the task incorrectly and talked through how they could be corrected. The child was then handed the activity and encouraged to slowly perform the task using the sequences modelled by the therapist whilst using the same verbalisations, or verbalisations the child had developed. These verbalisations during task performance have been referred to as verbal mediation. The mediators serve to teach the child how to comprehend a task, direct motor movement through self commands and importantly, to guide, monitor and control their own performance [111]. If the child had difficulty performing a previously practiced task, the therapist prompted the child using recall of verbal mediators (see Figures 4 and 5). Importantly, this technique was demonstrated and reinforced to parents to ensure a similar process is undertaken in the home environment.

**Figure 4 F4:**
[figure not shown]
Development of grasp, hold and release using verbal mediators

**Figure 5 F5:**
[figure not shown]
**Development of stability of grip using a cognitive-motor approach to treatment**.

Identifying and breaking down the specific sequences of a task allowed the therapist to assist the child to discover deficient sequences and to prompt them to consider the error before the end of the whole task. This inhibits failure of the task at an incipient stage thereby reducing the likelihood that the child will become frustrated or non-compliant [111]. Typically, children become more motivated if they have been active and successful participants in the problem solving process. Over time, this approach aims to promote a child's resilience by independently prompting themselves to identify incorrect sequences before becoming angry or frustrated. With proficiency in performance the need for self-rehearsal diminishes [111]. Importantly, the child learns how to learn. In an attempt to facilitate generalisation of the learning, task practice in this RCT was encouraged in various environments (i.e. using home programs) and with different activities that required similar strategies [110].

### Statistical analysis

Data were managed and analysed using the Statistical Package for Social Sciences (SPSS version 16.0). Descriptive statistics were calculated to summarise the data set for both groups and to identify potential baseline differences between the groups; *p *values were used to indicate the strength of the evidence and will be interpreted according to Sterne and Davey Smith [112] Distributions of data from each group and for each occasion were assessed to determine if they met the assumptions for the various inferential analyses.

#### Testing the effectiveness of therapy (Hypotheses 1 and 2)

Using continuous, interval level data from the AHA, differences between the two groups were assessed using a linear regression approach to analysis of covariance (ANCOVA). This controlled for the covariates of baseline AHA scores and the child's age. These variables were included as covariates as they might provide alternative explanations for any observed changes in scores. The size of treatment effect was estimated by comparing differences in group means and their 95% confidence intervals. Regression analyses and scatter-plots were used to investigate the relationship of post-treatment outcome with initial deficit.

#### Testing the effect of therapy on secondary outcomes (Hypothesis 3)

Between group differences were assessed using ANOVA for continuous data (following tests of normality). Outcomes that had non-continuous data or did not meet usual assumptions of linear regression were investigated using non-parametric statistics.

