### Outcome measures

Outcomes measures were completed on four occasions: baseline (1 to 2 weeks prior to injection), and at 1, 3 and 6 months after injection. Outcomes included measures from across the International Classification of Functioning, Disability and Health (ICF) [18] spectrum and involved a combination of investigator observed and parent report measures (See Table 1). This enabled analysis of the impact of intervention across the body function and activity domains.

**Table 1 T1:** Outcomes classified according to International Classification of Functioning, Disability and Health (ICF)

Body Function	Activity	
	
	Capacity	Performance
modified Tardieu Scale (MTS), modified Ashworth Scale (MAS), Quality of Upper Extremity Skills Test (QUEST; dissociated movement subscale)	Quality of Upper Extremity Skills Test (grasps subscale)	Assisting Hand Assessment (AHA), Canadian Occupational Performance Measure (COPM), Goal Attainment Scaling (GAS), Pediatric Evaluation of Disability Inventory (PEDI), Pediatric Motor Activity Log (PMAL)

The effects of upper limb BoNT-A injection in both groups were monitored using measures of muscle spasticity and muscle tone including the Modified Ashworth Scale (MAS) and Modified Tardieu Scale (MTS).

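### Normality tests choose between ANOVA and an unnamed rank-type test for the continuous secondary outcomes, and nothing holds one method per outcome across visits

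*Protocol article*

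**What the plan says.** Three statements in the Statistical analysis part of the protocol article bear on this.

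- The section on secondary outcomes (Hypothesis 3) makes ANOVA conditional: "Between group differences were assessed using ANOVA for continuous data (following tests of normality").
- The next sentence gives the fallback: "Outcomes that had non-continuous data or did not meet usual assumptions of linear regression were investigated using non-parametric statistics". Neither the normality test, its threshold, nor the non-parametric method is named.
- The opening paragraph of Statistical analysis says what was inspected: "Distributions of data from each group and for each occasion were assessed to determine if they met the assumptions for the various inferential analyses".

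The Outcome measures section sets the visits: "baseline (1 to 2 weeks prior to injection), and at 1, 3 and 6 months after injection". For the primary outcome, the section on Hypotheses 1 and 2 takes a different course. It fixes one method in advance ("differences between the two groups were assessed using a linear regression approach to analysis of covariance (ANCOVA"), with baseline score and age as covariates, and one effect measure: "The size of treatment effect was estimated by comparing differences in group means and their 95% confidence intervals".

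**The concern.** Read together, the statements describe a test-then-choose rule: look at the distributions, then select the method. Two things follow.

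First, the observed data choose the quantity being compared. ANOVA compares means in the units of the scale, while a rank method compares orderings. An outcome that lands on one side of a normality threshold answers a different question from one that lands on the other.

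Second, inspection is by group and by occasion, and the text does not say what happens when one occasion fails and the others pass. One permitted reading is that the method is then chosen visit by visit. The 3- and 6-month results for one outcome might then rest on different methods, and a change in p value between them could reflect the change of test. That matters in a trial whose stated aims (opening of Methods/Design) include evidence on retention of treatment effects.

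At least six scores are exposed: QUEST grasp and dissociated movement, PEDI self-care functional skills and caregiver assistance, and COPM performance and satisfaction.

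**Working it through.** The document gives no figure for this rule, so there is none to reproduce. The check asks how often the rule would move an outcome or a visit to a rank method when nothing is wrong with the data.

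**Inputs from the protocol article**
- Children per arm: 17 (Sample Size) to 20 (half of the 40 to be recruited).
- Groups: 2. Post-injection occasions: 3 (1, 3 and 6 months).

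**Assumptions, because the document names none**
- Shapiro-Wilk at 5% in each group at each occasion.
- A visit goes to the rank method if either group fails.
- Correlation between occasions 0.5 to 0.9.

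**Step 1: hand calculation, exactly normal data, independent checks**
- One visit is moved: 1 − 0.95² = 9.75%.
- The 3- and 6-month methods differ: 2 × 0.0975 × 0.9025 = 17.6%.
- At least one of the three post-injection visits is moved: 1 − 0.95⁶ = 26.5%.

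Correlation between visits lowers the last two figures, so simulation is needed.

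**Step 2: simulation (3,000 runs per setting; ranges over 17 and 20 per arm and correlations 0.5, 0.8 and 0.9)**

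| Shape of the data | One visit moved | Any of 3 visits moved | 3 visits not all the same method | 3- and 6-month methods differ |
|---|---|---|---|---|
| Exactly normal | 9-10% | 21-26% | 20-26% | 13-18% |
| Mild skew (lognormal, sigma 0.25) | 29-34% | 50-70% | 38-65% | 25-44% |
| More skew (lognormal, sigma 0.4) | 53-62% | 77-94% | 42-70% | 28-47% |

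A separate simulation with correlations up to 0.9 gave 3- and 6-month disagreement of about 12-18% for normal data and about 24-40% for a mild ceiling (Beta(5,2) shape), which is plausible for bounded 0-100 scores.

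**Step 3: how informative is one test?** With mild skew, a visit is flagged in 29.4% to 33.9% of runs when either of two groups can flag it. Per group, that is 1 − √(1 − 0.294) = 16% to 1 − √(1 − 0.339) = 19%. The test misses this departure in more than four groups out of five, yet it flags 5% of perfectly normal groups.

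**Step 4: the outcome-level reading.** Suppose any failed post-injection visit moves the whole outcome. With exactly normal data, 21-26% of outcomes are moved. Over six scores the expected number moved is 6 × 0.21 = 1.3 to 6 × 0.26 = 1.6. No outcome then changes method between visits, but the six scores are reported on a mix of effect measures chosen by chance.

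**Step 5: error rates.** With a Mann-Whitney test assumed as the fallback and 18 per arm, simulated Type I error stays at 4.3-6.2%. For the unadjusted ANOVA as written, power is hardly changed by adding the switch.

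**The case against.** The strongest reply is that visit-by-visit switching is not stated. The opening paragraph says only that distributions were assessed, for all analyses, and the Hypothesis 3 section speaks of outcomes that fail. The natural unit of switching may therefore be the whole outcome. This stands: the switch between 3 and 6 months is one reading, not a stated procedure. The data-driven choice of method remains on either reading (step 4).

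A reader might also infer three stronger faults. The document does not support them.

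- *That the wrong distributions are checked.* The stated secondary analysis is ANOVA with no covariates. At a given visit its residuals are the group data minus the group mean, so checking each group is checking the residuals. The criticism would apply only to a covariate-adjusted model.
- *That switching throws away baseline adjustment and power.* The Hypothesis 3 section states no such adjustment, so a rank test loses none. A large power loss appears only for a hybrid of ANCOVA and a rank test that the document does not describe.
- *That no effect estimate will be given.* The Hypothesis 3 section is silent on this, and a condensed article may leave it to a fuller plan.

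Finally, a rank method for COPM, an average of parent ratings from 1 to 10, is defensible. That argues for settling the method by the nature of the scale, not by a normality test.

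**Conclusion.** The point holds in a limited form. The protocol article lets tests of normality decide whether each continuous secondary outcome is compared by ANOVA or by an unnamed non-parametric method, and it has no rule keeping one method per outcome across visits. The harm is to interpretation: the estimate is chosen by the data and may not be comparable across outcomes or, on one reading, across visits. The validity of the tests is not in question, since Type I error stays near 5% and the power of the ANOVA as written barely moves.

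The percentages depend on a mechanical Shapiro-Wilk test at 5%, on any single failure triggering the switch, and on the assumed shapes and correlations. A more lenient use of the checks would switch less often. The outcomes are secondary, and the primary AHA analysis has its method named in advance, so this is a change that should be made and not one on which the trial's main conclusion turns.

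**What to change.** In the Hypothesis 3 section, delete the parenthesis that makes ANOVA depend on normality testing, and assign the method by outcome type.

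- For QUEST grasp and dissociated movement, the PEDI self-care scaled scores, and COPM performance and satisfaction: one linear model, the same at every visit. The simplest choice is the form already used for the AHA, with the outcome's own baseline and age as covariates. Report the mean difference with its 95% confidence interval, inspect residual plots, and give a bootstrap interval or permutation p value as a sensitivity analysis.
- For outcomes that are ordinal or discrete by construction (the modified Ashworth Scale, the Tardieu grade, the proportion of goals achieved): a named rank, ordinal or otherwise suitable method, again the same at every visit.

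The Current study status section says analysis is already under way. If secondary comparisons have been seen, report every visit under the single model and state when that choice was made.

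The cost is about two sentences of wording and one resampling run per outcome, with no new data. The downside is that the model-based interval is only approximate for a strongly skewed outcome, which the sensitivity analysis covers.

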#### Testing the clinical significance of the effect of therapy on primary outcome (Hypothesis 4)

The magnitude of treatment effect was evaluated relative to defined criterion of clinical significance.

#### Testing the effect of age and intensity of therapy (Hypotheses 5 & 6)

Data related to the number of minutes spent by all children undergoing treatment was extracted from the log book for each child. Associations between the intensity of therapy and outcome and age of children and outcome were determined, while controlling for the covariate of group, using ANCOVA.

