### Secondary objectives

A. To compare the effect of modified CIMT versus bimanual occupational therapy (BOT) on secondary outcomes relating to: the performance of activities of daily living; the quality of upper limb movement; occupational performance; individual goal achievement; and frequency of use of the affected upper limb of children with hemiplegic cerebral palsy following upper limb BoNT-A injection.

#### Hypothesis 3

Modified CIMT is more effective than conventional BOT in improving performance of activities of daily living, quality of upper limb movement, occupational performance, individual goal achievement and frequency of use of the affected upper limb in children with hemiplegic cerebral palsy following upper limb BoNT-A injection.

B. To evaluate the clinical significance of change identified on the primary outcome, the Assisting Hand Assessment.

#### Hypothesis 4

That changes on the Assisting Hand Assessment associated with intervention are of a clinically significant magnitude. Clinical significance was defined as a change score of more than 5 raw score points (2.6 logits) on the AHA ([name], personal communication).

C. To evaluate the impact of age and actual treatment dosage on the primary outcome, the Assisting Hand Assessment.

#### Hypothesis 5

Younger children (irrespective of treatment type) will show greater improvement in bimanual performance following uni-manual or bimanual therapy and upper limb BoNT-A injection.

#### Hypothesis 6

Children who undertake treatment of greatest intensity (irrespective of treatment type) will show greater improvement in bimanual performance.

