#### Movement-based therapy: General Considerations

One-month following injection of BoNT-A, children randomised to the experimental group received modified constraint-induced movement therapy (mCIMT). Children randomised to the control group received conventional bimanual occupational therapy (BOT). The individual-based treatment sessions of 45 to 60 minutes were conducted by the same occupational therapist ([name]) twice weekly for 8 weeks in an outpatient paediatric treatment room. In addition, children in the mCIMT experimental group were required to complete 3 hours of home program (with the mitt on), 7 days a week for the 8 week treatment period. Children in the BOT control group were also encouraged to undertake a home program but no time requirements were specified. A checklist was completed after each treatment session, identifying the activities used and general observations. Important general considerations for both groups related to establishing and maintaining rapport, equipment, preparing and implementing the sessions are described below.

Building rapport and establishing the therapist-child/therapist-parent relationship was a primary focus for initial treatment sessions. Along with identifying individual movement, hand skill and motor planning abilities of each child, this time allowed for selection of toys to match the demands of the task with the child's developmental level and specific hand skill goals. It was also necessary to establish expectations for future sessions, create an understanding of acceptable behaviour and to establish patterns of on-task behaviour for the child.

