#### Constraint-induced movement therapy

The modified constraint-induced movement therapy (mCIMT) protocol incorporated the two fundamental components of CIMT as described by Taub et al. [36]: the use of a restraint device (glove) and; the provision of massed practice to the affected upper limb (3 hours of home program). A comfortable neoprene (wet suit material) glove was worn on the hand of the non-affected upper limb to facilitate intensive practice of the affected upper limb. The neoprene glove, with a palmar thermoplastic insert over the fingers and thumb to prevent grasp, allowed the child to use the hand as an effective assist in bilateral activities, but did not allow active grasp of objects (see Figure 2). Importantly, the glove allowed the child to use the unaffected limb for breaking a fall, if needed. The intervention period was 2 months and involved wearing the glove 7 days per week. Children were expected to wear the glove for 3 hours per day, including therapy time and the home program, which could be split into different sessions of no less than 30 minutes duration. Families were expected to undertake an intensive home program of 3 hours per day. This could occur in the child's usual environment including home, crèche, preschool or school. Caregivers completed a log-book detailing the total period the restraint device was worn per day and any issues arising from use of the glove. The intention of the home program was to facilitate an intensive period of practice with the affected limb and to educate, empower and include families and caregivers in the treatment process. Families were provided with written and specific goals by the treating therapist after each session. These were based around development of specific hand skills such as grasp, hold, release, reach, in-hand manipulation. Families were encouraged to focus on these goals during the home program. Families were discouraged from placing the glove on the child without supervision to avoid frustration.

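### The Hypothesis 6 dose analysis, as most naturally read, adjusts for group but not for age, so an age effect on AHA change could pass for, or hide, a dose response

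*Protocol article*

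**What the plan says.** Two hypotheses under secondary objective C concern who improves on the AHA, whichever treatment they receive. Hypothesis 5: "Younger children (irrespective of treatment type) will show greater improvement in bimanual performance". Hypothesis 6: "Children who undertake treatment of greatest intensity (irrespective of treatment type) will show greater improvement in bimanual performance".

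Both are analysed in one short section, Testing the effect of age and intensity of therapy (Hypotheses 5 & 6). The dose variable is defined there: "Data related to the number of minutes spent by all children undergoing treatment was extracted from the log book for each child". The same section then states that associations of intensity with outcome and of "age of children and outcome were determined, while controlling for the covariate of group, using ANCOVA". Group is the only covariate named.

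The section on Hypotheses 1 and 2 names more for the same outcome: "This controlled for the covariates of baseline AHA scores and the child's age". It gives the reason: "These variables were included as covariates as they might provide alternative explanations for any observed changes in scores".

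**The concern.** The article treats age as a rival explanation for AHA change in the between-group comparison, where randomising in age-matched pairs already tends to balance age. It does not name age in the dose analysis, where nothing balances it. Minutes arise after randomisation from what each family and child do. Matching equalises age between arms. It does nothing to equalise age between children with many and few minutes inside an arm.

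Confounding by age needs two links. Age to outcome is the trial's own Hypothesis 5. Age to minutes is not stated anywhere, but it is plausible: ages run from 18 months to 6 years, and the bimanual occupational therapy (BOT) home programme was left open ("Children in the BOT control group were also encouraged to undertake a home program but no time requirements were specified").

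If younger children improve more and also log more minutes, a dose response appears where there is none. If older children log more minutes, a real dose response is reduced or cancelled. The aim stated at the start of Methods/Design includes evidence on dose response, so this slope is a result that readers would use.

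**Working it through.** **The plan's own figure.** The article gives no figure for Hypothesis 6. The only relevant one is the sample size: 17 per group for 2.6 logits at 80% power. The SD, alpha and sidedness are not given, so 17 cannot be reproduced independently, but it can be solved for the SD. At two-sided 0.05:

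SD = 2.6 / [(1.960 + 0.842) × √(2/17)] = 2.6 / (2.802 × 0.343) ≈ 2.7 logits.

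At one-sided 0.05 it would be about 3.05. Whether this is the SD of change or of a follow-up score is not stated. It serves here only as a scale for the residual.

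**Assumed inputs (not in the documents).**
- Age uniform over 1.5 to 6 years, so SD = 4.5/√12 = 1.30 years.
- Age slope of AHA change from -0.3 to -0.8 logits per year, the direction of Hypothesis 5.
- Within-arm correlation r of age with minutes from 0.2 to 0.6, in either direction.
- Residual SD 2.7 logits (from the sample size, as above) or 1.5 logits (assumed).
- 36 children in two arms, between the 34 required and the 40 targeted.

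**Bias of the group-only dose slope.** With age left out, the bias per SD of minutes has absolute size |age slope| × 1.30 × |r|:

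| Age slope (logits/year) | r = 0.2 | r = 0.4 | r = 0.6 |
|---|---|---|---|
| -0.3 | 0.08 | 0.16 | 0.23 |
| -0.8 | 0.21 | 0.42 | 0.62 |

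Simulation gives the same range, up to about 0.64. The bias is positive if younger children log more minutes and negative if older children do. It is zero if r = 0.

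**False-positive rate with no true dose effect.** AHA change was simulated as age slope × age plus normal error. It was then regressed on minutes and group, with and without age, and tested at two-sided 0.05.
- Group only, SD 2.7: about 5% to 25%.
- Group only, SD 1.5: about 6% to 53%.
- With age added: about 5% throughout.

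**Cross-check on a standardised scale.** With N = 34 or 40, age-minutes correlations of 0.3 or 0.5, and age-improvement correlations of 0.3 or 0.5, the group-only rate is 8% to 34%. With age in the model it is about 5%.

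**Masking.** Take a true dose effect of 0.5 logits per SD of minutes, with older children logging more. At r = 0.4 to 0.6 the group-only estimate runs from 0.5 - 0.16 = 0.34 down to 0.5 - 0.62 = -0.12. With age included it is 0.5. At SD 1.5, power is 5-24% without age and 32-40% with it.

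**Precision cost of adding age.** The standard error of the minutes slope grows by 1/√(1 - r²), which is 1.09 at r = 0.4 and 1.25 at r = 0.6. At SD 1.5 this takes 0.27 to about 0.29 and 0.34. At SD 2.7 those become 0.29 × 1.8 = 0.52 and 0.34 × 1.8 = 0.61 (2.7/1.5 = 1.8). An effect of 0.5 would then be hard to detect in any model.

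**The case against.** **The sentence may mean one model.** A single heading and a single sentence cover age and intensity, so both could have been entered together with group controlled. Hypothesis 6 would then already be age-adjusted. This reading is possible but less natural: the sentence lists two separate associations and names one covariate, in the singular. A reader might go on to infer that the joint model would spoil Hypothesis 5, because the age effect would be conditional on minutes. That goes too far. Hypothesis 5 does not say whether it means a total age effect or one at fixed dose, so the wording needs settling but is not an error on that account.

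**The link from age to minutes is not documented.** This stands. A reader might take the modified CIMT section as evidence, since home practice could happen in settings "including home, crèche, preschool or school". That text says where practice may take place, in one arm only, and says nothing about minutes varying with age. The home prescription in that arm is 3 hours a day for every child, and clinic sessions are scheduled alike in both arms. Adherence can still differ by age, and BOT home time is open, but a correlation of 0.4 to 0.6 is an assumption.

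**The upper figures are extreme.** This also stands. A slope of -0.8 logits per year spans 0.8 × 4.5 = 3.6 logits over the age range, more than the 2.6 logits that the trial calls clinically significant. The Background reports that response to CIMT does not appear to depend on age, and the grid has no slope weaker than -0.3. The article also uses p values as strength of evidence and sets no 0.05 threshold, so the false-positive rate illustrates the problem and is not the plan's decision rule. The bias in the slope does not depend on any threshold.

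**It is a condensed article about a secondary aim.** True, but the article does name the covariate set here, and it differs from the set that the article justifies for the same outcome.

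**Conclusion.** The point holds at modest size. As most naturally read, the dose analysis omits a variable that the article itself regards as a rival explanation for AHA change, and age-matched randomisation does not supply the missing control. The dose slope is confounded if minutes vary with age within an arm and age affects improvement. Both conditions are needed, and the documents state only the second, as a hypothesis.

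Of the two sets of rates, the one at SD 2.7 has some footing in the article's sample size, given two-sided 0.05. The upper end at SD 1.5 needs the steepest slope, the strongest correlation and the smaller SD together.

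A reader might infer that the reported dose response will be false, or that its direction of error is known. The documents support neither. Only secondary objective C is affected. Even with age in the model, the dose result stays observational.

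**What to change.** Replace the single sentence with two stated models:
- Hypothesis 6: AHA outcome on minutes, group, age and baseline AHA, which adds minutes to the covariates of the primary model.
- Hypothesis 5: AHA outcome on age, group and baseline AHA, without minutes.

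This settles the one-model or two-model ambiguity and also brings in baseline AHA, which the present sentence does not name either. Because the article says that analysis is under way, the date of the change should be recorded, with a note of whether the dose results had been seen. The report should give the within-arm correlation of age with minutes, so that readers can judge how much the adjustment matters, and should describe the dose finding as observational.

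The cost is a few lines of text and no new data. Adding age takes one degree of freedom and widens the interval for the minutes slope somewhat when age and minutes are correlated. If they are uncorrelated, almost nothing is lost.
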